## Abstract

**Background:**

Dengue is the most common and widespread mosquito-borne arboviral disease globally estimated to cause >390 million infections and >20,000 deaths annually. There are no effective preventive drugs and the newly introduced vaccines are not yet available. Control of dengue transmission still relies primarily on mosquito vector control. Although most vector control methods currently used by national dengue control programs may temporarily reduce mosquito populations, there is little evidence that they affect transmission. There is an urgent need for innovative, participatory, effective, and locally adapted approaches for sustainable vector control and monitoring in which students can be particularly relevant contributors and to demonstrate a clear link between vector reduction and dengue transmission reduction, using tools that are inexpensive and easy to use by local communities in a sustainable manner.

**Methods:**

Here we describe a cluster randomized controlled trial to be conducted in 46 school catchment areas in two townships in Yangon, Myanmar. The outcome measures are dengue cases confirmed by rapid diagnostic test in the townships, dengue incidence in schools, entomological indices, knowledge, attitudes and practice, behavior, and engagement.

**Conclusions:**

The trial involves middle school students that positions them to become actors in dengue knowledge transfer to their communities and take a leadership role in the delivery of vector control interventions and monitoring methods. Following this rationale, we believe that students can become change agents of decentralized vector surveillance and sustainable disease control in line with recent new paradigms in integrated and participatory vector surveillance and control. This provides an opportunity to operationalize transdisciplinary research towards sustainable health development. Due to the COVID-19 pandemic and political instability in Myanmar the project has been terminated by the donor, but the protocol will be helpful for potential future implementation of the project in Myanmar and/or elsewhere.

Registration: This trial was registered in the ISRCTN Registry on 31 May 2022 (
https://doi.org/10.1186/ISRCTN78254298).

## Introduction

Dengue is the most common mosquito-borne arboviral disease in the world with an estimated >390 million infections and >20,000 deaths annually and about 2.5 billion people living in risk areas
^
1
^. Dengue is caused by a flavivirus (DENV) consisting of four serotypes which offer no cross-protective immunity, meaning that an individual can contract dengue fever up to four times in a lifetime. Dengue and other arboviruses, such as Zika and chikungunya, are transmitted primarily by the
*Aedes aegypti* mosquito vector, which breeds preferentially in artificial water containers near human habitation.
*Aedes albopictus* is considered a secondary vector, more abundant in rural areas. Both vectors are day-biting mosquitoes
^
2
^. A tetravalent dengue vaccine has been developed but offers only incomplete protection and is associated with adverse events in seronegative individuals
^
3
^. As there are no current therapeutic and preventive drugs available
^
4
^, vector control remains the primary method to prevent DENV transmission. Vector control with a focus on the most productive, and hence epidemiologically important, mosquito breeding sites is cost-effective, especially in resource-constrained settings and in disease hotspot areas
^
5,
6
^. This requires a sound knowledge of local vector ecology, household water management practices, and spatial variations in disease patterns.

The incidence of reported dengue doubles approximately every decade
^
7
^, with estimates being highly uncertain due to a range of factors which change over time including diagnostic criteria, access to health services and coverage and quality of surveillance systems. In the 1960’s, dengue was present in nine countries, but today occurs in at least 128 countries
^
8
^. The global and local driving forces responsible for this increase are rapid, unplanned, and unregulated urban development, globalization, population growth, climate, inadequate municipal services, insecticide resistance, and lack of sustainable and integrated interventions that account for the complexities of ecological and social systems
^
9–
12
^. Despite increased research and knowledge about factors affecting transmission of arboviruses, effective and sustainable disease control is still lacking. Disease and vector control have long relied on vertically structured single interventions with limited or nonexistent community involvement without recognizing the importance of complex adaptive social-ecological systems that includes pathogen-vector-host-environment relationships
^
9,
13
^. There is a compelling need for integrated, innovative, effective, and locally adapted approaches for sustainable vector control. Engaging schools and students and promoting ownership of disease control interventions have high potential for achieving sustainable change to reduce dengue transmission as engaged local actors can sustain interventions after an externally funded project terminates ensuring continuity of project outcomes.

Infectious diseases, such as those caused by arboviruses, are likely to spread easily in schools due to frequent contact of students with infective resident mosquitoes breeding in and near the school
^
14,
15
^. Students are disproportionately exposed to the day-biting habits of
*Aedes* mosquitoes compared to other age groups. A study in Mexico revealed that students, teachers, and other personnel were more likely to be exposed to DENV-infected
*Ae. aegypti* females on school premises
^
14
^. Schools also provide a cost-effective entry point for dengue prevention and control that can enhance community-wide vector control through knowledge transfer from schools to communities
^
16
^. A combination of vector control tools and pedagogical approaches can improve knowledge uptake as well as knowledge and technology transfer from classrooms to homes
^
16
^. This is important because dengue predominantly affects children
^
2
^, and vector control measures such as mosquito source reduction require constant household and community engagement.

Schools have been engaged in national dengue control programs in several countries and school-based vector control trials have been associated with increased dengue knowledge
^
17,
18
^, improved prevention/control practices in schools
^
17,
19
^, and contributed to improved school and community-based vector control activities
^
18
^. A trial in Colombia showed that schools receiving sets of interventions targeting dengue (and diarrhea) risk factors reduced mosquito breeding in the schools and significantly improved knowledge in children
^
19,
20

^. Outbreaks were recorded in 2009 (22,400 cases), 2013 (20,255 cases and at least 75 deaths), and 2015 (43,845 cases and 140 deaths)
^
29
^. A dengue outbreak occurred in 2017 with 31,000 cases and 192 deaths at the national level
^
30
^. In 2019, Myanmar also experienced an outbreak of chikungunya, with several cases recorded in travelers to the country
^
31
^. In Myanmar, there are more than 45,000 schools with eight million students, making up approximately 17% of the population
^
32
^. Most cases of dengue in Myanmar, occur in children under 15 years old, especially those in the 5–9-year age group
^
33–
35
^. At the time of planning this study, one objective of the National Strategic Plan for Dengue Prevention and Control of Myanmar was to develop a comprehensive integrated training manual and guidelines including community and school-based vector control
^
27
^. This has led to the
*Aedes*-free school program, which includes educational and practical activities.

Considering the global increase in dengue, effective dengue control should not rely on traditional insecticide-based, silver-bullet, top-down approaches
^
36,
37
^. Simple single-intervention approaches as practiced in the past were not successful, for example larval source reduction or fogging. Suitable combinations of site-specific, effective, acceptable, and sustainable interventions need to be assessed for each situation
^
38
^. Therefore, we developed the current project for urban communities in Yangon, Myanmar. We aim to reduce dengue incidence and entomological risk factors, and improve knowledge, attitudes, and prevention practices by applying innovative combinations of school-driven non-insecticidal vector control tools, educational and knowledge transfer approaches by enhancing the school curriculum, building teachers’ capacity; and communicating behavioral change and transfer of knowledge following previous guidelines and recommendations
^
25,
36,
37,
39
^. A process evaluation will be conducted to supplement and strengthen the impact evaluation and to understand the processes and mechanisms of the interventions that can help explain impact or lack thereof.

## Methods

### Objectives and hypotheses

The overall objective of this trial is to assess the impact of student-driven interventions on dengue incidence, mosquito indices and dengue knowledge, attitudes and prevention practices in schools and communities.

The specific project objectives are to

1. Reduce dengue incidence in schools and communities.2. Reduce entomological indices in schools and communities.3. Improve knowledge of dengue, entomology, and vector control in students and their parents.4. Engage students, teachers and relevant stakeholders in community vector control and monitoring.5. Facilitate improved teaching capabilities by training of teachers and enhancing the dengue school curriculum.6. Determine implementation fidelity and adaptation of interventions through process evaluation.

The main hypothesis of the study is that the dengue incidence rate will be lower in the intervention arm compared to the control arm. Other hypotheses are that mosquito indices will be lower; and that there will be improvements in the knowledge, attitudes and practices (KAP) regarding dengue risk reduction and community engagement in vector control activities in the intervention arm compared to the control arm.

### Trial design

This cluster randomized controlled trial (RCT) is designed to study the effect of integrated entomological and educational interventions on dengue incidence, adult dengue mosquito density and KAPs regarding dengue risk reduction among students and parents in two townships in Yangon, Myanmar. The rationale for a cluster design is that interventions are area-wide in character, since they will be implemented in schools, rather than targeting individuals. It is not feasible to randomize some individuals within a school to one intervention and other individuals to another. Schools (clusters) will be randomized into an intervention arm and a control arm.

### Study setting and participants

The study is planned to be conducted in South Dagon and Shwepyithar townships in Yangon Region, Myanmar (
Figure 1). These townships were selected out of the 45 in Yangon because of high dengue incidence and absence of other dengue projects. The population in South Dagon is ca. 307,000 and in Shwepyithar ca. 287,000. During 2013–2018 there were a total of 1,465 reported dengue cases (mean 244/year) and 15 deaths in South Dagon and 1,420 cases (237 cases/year) and eight deaths in Shwepyithar. These two townships represented approximately 12% of all reported dengue cases in Yangon Region during this period. There are 46 middle schools and high schools in these two townships, 20 in South Dagon and 26 in Shwepyithar. In 2019, there were an average of 250 sixth grade students per school. 40 high or middle schools will be included in the study (
Table 1). In each school approximately 40 sixth grade students (1–2 classes) will be selected based on feasibility, logistics, and willingness to participate. Each school and its catchment area (buffer zone) will be mapped. Non-overlapping school catchment areas that include students’ households represent the study clusters. Eligibility criteria are described in
Table 1. The delineation of school catchment area will consider mosquito flight distance from schools, but also providing sufficient buffer zones between adjacent catchment areas to avoid contamination between intervention and control schools. It is anticipated that a minority of students (<10%) will live in a different school catchment area within the two study townships. Due to the current health and security situation in Myanmar, the project has been terminated by the donor, but the protocol forms a basis for future implementation in Myanmar or elsewhere.

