**Figure 1. f1:**
[figure not shown]
Map of study sites in Yangon, Myanmar. Data Source: Ministry of Education, Myanmar.

**Table 1. T1:** Eligibility criteria.

	Inclusion criteria	Exclusion criteria
**Schools**	- High and middle schools in selected townships in Yangon. - Schools that have at least 40 6 ^th^ grade students. - Approval by headmaster of school through signed informed consent and Letter of Agreement. - Approval by relevant teachers by signed informed teacher consent.	- Schools with other ongoing dengue interventions. - Schools with classes with fewer than 40 6 ^th^ grade students - International schools not using the national curriculum and Burmese as language of instruction. - Boarding schools.
**Students**	- Students who will start 6 ^th^ grade in June Year 1. - Signed informed assent. - Signed informed consent by parents.	- Students who are seriously ill and not considered physically fit to participate. - Students whose parents do not provide consent.

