### Interventions

The interventions consist of integrated sets of vector control and educational/knowledge transfer interventions that will be implemented simultaneously. The justification for implementing sets of interventions instead of single interventions is the growing consensus that single interventions are not sufficient to control vector borne diseases because of the complexity of the transmission systems and their components
^
37,
40
^. Vector control tools must also be integrated with educational interventions and knowledge transfer to achieve sustainable change. Interventions will be implemented in schools and communities by students and teachers with project staff overseeing the quality and coverage of the interventions as part of the process evaluations (see below). Interventions will commence at the start of the school year (June Year 1). No interventions will be implemented in the control arm. However, schools and communities may receive control activities carried out by the national dengue control program. These schools also receive standard dengue control instructions from the School Health Division.

The vector control intervention has four components: (1) Adult mosquito mass trapping using commercial oviposition traps (Gravid Aedes Trap (BG-GAT)
^
41
^ and locally produced traps (plastic bottles) constructed by students will be placed in both schools (10 per school) and a ample of 40 students’ households (one per household). Homemade traps will also be distributed to the communities by students. (2) Larval control using larvivorous guppy fish (
*Poecilia reticulata*). Guppy fish will be placed in suitable water storage containers in schools and households. Guppy fish production facilities (5 jars per school) will be set up in intervention schools, and students will learn how to manage these, propagate new fish, and distribute fish to their households and communities. (3) Prevention of mosquito breeding using tightly fitting lids or covers for water storage containers made of tarpaulin or other locally produced materials. These will be distributed to all intervention schools and 40 associated households per school. (4) Source reduction by weekly solid waste management and cleanup campaigns by students around their schools and households. This intervention require provision of garbage bags, protective gear and other material.

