### Data analyses

**
*Effect of intervention on primary outcome*
**

1. 
**Dengue incidence rate in communities (DI).** The total cumulative number of dengue cases in the communities will be recorded passively through patients presenting at collaborating public hospitals and health centers in the two townships. Each case will be confirmed by dengue antigen/antibody RDTs. Each case that resides in the school catchment areas will be noted as such. The denominator will be the estimated population in each school catchment area. Data analysis for the primary outcome will be a comparison of the overall difference in incidence rate of confirmed dengue cases between the intervention and non-intervention school catchment areas with sub-analyses comparing the monthly incidence over time, before, during and after the interventions to examine the timing of any intervention impact. Incidence data will be collected continuously over a one-year period. At the cluster level, analysis will be by intention to treat, i.e., taking the trial arm as that to which, each cluster was randomized. At the individual level, people will be taken to have the allocation of the arm in which they are resident at the time of any data contributed. A flowchart showing numbers of clusters, and average numbers of households per cluster, over time will be constructed in accordance with Consolidated Standards of Reporting Trials (CONSORT) guidelines
^
66

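### Students living in another school's catchment are eligible and receive household materials, so some materials land in the opposite arm, and the arm for school seroconversion is left unclear

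*Protocol article*

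**What the plan says.** Study setting and participants defines the clusters geographically: "Non-overlapping school catchment areas that include students’ households represent the study clusters". Protection against spill-over is also geographic, by "providing sufficient buffer zones between adjacent catchment areas to avoid contamination between intervention and control schools". The same paragraph then says: "It is anticipated that a minority of students (<10%) will live in a different school catchment area within the two study townships".

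Table 1 admits students by grade, assent and parental consent. It excludes only serious illness and "Students whose parents do not provide consent". Where the student lives is not a criterion.

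Interventions places one trap in each of 40 students' households per intervention school. Of lids and covers it says: "These will be distributed to all intervention schools and 40 associated households per school". Students also take fish home and pass fish and homemade traps on to their communities. None of this is limited to homes inside the school's own catchment.

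Data analyses, item 1 (dengue incidence in communities), keeps clusters in their randomised arm. For individuals it says that "people will be taken to have the allocation of the arm in which they are resident at the time of any data contributed".

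**The concern.** The cluster definition and the buffers assume that a student's school and home share a catchment. For the students just described they do not, and a buffer between two catchments cannot stop a student from carrying a trap home across it. A student at an intervention school who lives in a control catchment is taught in one arm and takes materials into the other. By residence, that student counts as control. A control-school student living in an intervention catchment carries nothing across, but by residence would count as intervention.

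Two things are at stake. Intervention materials are placed inside control areas, which is avoidable. And for outcomes measured on students or in their homes, the arm assigned may differ from the arm that delivered the exposure, which biases the comparison towards no difference.

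**Working it through.** **1. The plan's own figure.** Sample size states more than 80% power for a 30% reduction. Its inputs are 23 schools per arm, 40 person-years per school, rates 10.5/40 = 0.2625 and 7.35/40 = 0.18375, intra-cluster correlation 0.01 and α = 0.05 (taken as two-sided).
- Design effect: 1 + 39 × 0.01 = 1.39. Effective size: 920/1.39 = 662 per arm.
- Power: 93% (two proportions), 86% (Poisson rates with the same design effect), 88% (cluster-rate formula with between-cluster coefficient of variation √(0.01 × 0.7375/0.2625) = 0.168).

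The claim reproduces. It is not used further here, because its base is 40 person-years per school, whereas the primary outcome uses the catchment population.

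**2. Which arm each outcome takes.**

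| Outcome | What the protocol says | Arm for a student whose school and home are in different arms |
|---|---|---|
| Community incidence | Data analyses, item 1: residence | Home; defensible for an area outcome |
| Student KAP | Item 8: school averages, compared by whether the school had the intervention | School |
| Parent KAP | Item 9: as for students | School |
| SR_S | Item 2: counts per cluster; Data collection samples within each school | Unclear: a cluster is a school in Trial design and a catchment in Study setting |
| Household seroconversion (SR_H) | Data collection: 40 households per catchment, 20 of them students' homes | Home, if students' homes outside the catchment are left out; not stated |
| Household mosquito indices | Five of the selected households per cluster | As for SR_H |

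**3. Households that cross.** Inputs: 40 student households per school, 23 schools per arm, ceiling 10%. Once one catchment's arm is fixed, 23 of the other 45 are in the opposite arm.
- Intervention student households: 40 × 23 = 920.
- In another catchment, at the ceiling: 0.10 × 920 = 92.
- In the opposite arm: 92 × 23/45 = 92 × 0.511 = 47, or 47/920 = 5.1%.
- Per control catchment: 47/23 = about 2.

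**4. Primary outcome.** The townships have 307,000 + 287,000 = 594,000 people, so 594,000/46 = about 12,900 per catchment. Household size is not given. At an assumed 4 to 6 people, 2 households are 8 to 12 people, and 12/12,900 is under 0.1%.

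**5. Outcomes on students and their homes, if assigned by residence.** Let x be the share crossing, equal in both directions, with a true rate ratio of 0.70 in those exposed:

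observed ratio = [(1 − x) × 0.70 + x] / [(1 − x) + x × 0.70]

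- x = 0.051: (0.949 × 0.70 + 0.051)/(0.949 + 0.051 × 0.70) = 0.715/0.985 = 0.726, a reduction of about 27%.
- x = 0.026 (half as many students living elsewhere, or a sample of which only half are students' homes, as in SR_H): (0.974 × 0.70 + 0.026)/(0.974 + 0.026 × 0.70) = 0.708/0.992 = 0.713, a reduction of 28.7%.
- x = 0: the full 30%.
- x = 0.10 (every such home in the opposite arm): 0.73/0.97 = 0.753, a reduction of 24.7%. The lottery makes this extreme unlikely.

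The formula treats the whole effect as following the crossing student or household. It does not apply where the arm is taken from the school.

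**The case against.** The strongest reply is that the residence sentence stands under the primary outcome, where assigning people by area is a sound intention-to-treat rule. Items 8 and 9 analyse student and parent KAP by the school's arm. SR_S is sampled within schools, and its natural reading is also by school. The household sample is described by catchment, so a student's home elsewhere may never enter it. Residence is recorded for each sampled person, homes are mapped, and a detailed SAP is promised. Most of this stands, and it narrows the point to delivery, student-household samples and SR_S.

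Three stronger readings are tempting, and the documents do not support them.
- That KAP is misassigned: items 8 and 9 say otherwise.
- That the primary result is materially diluted, or that its power drops to around 80% or below: such figures come from applying the crossing share to 40 person-years per school. About 2 households in a catchment of about 12,900 people cannot do that.
- That the fall from 30% to 27% holds across the secondary outcomes: it needs assignment by residence and crossing in both directions, so it is a bound for the outcomes in step 5 only.

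What the reply does not answer is that household delivery is not tied to the catchment. Nor does it settle SR_S: the residence sentence covers any data contributed, and the protocol uses cluster in two senses.

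**Conclusion.** The point holds in limited form. The protocol expects students whose home is in another catchment, does not exclude them, and sends materials to their homes. At its ceiling this places about 47 of 920 intervention student households in control areas. The direct effect on community incidence is negligible; onward sharing of fish and homemade traps could add to it by an amount the document does not allow one to estimate. For student-household outcomes, and for SR_S if residence decides the arm, the bias is towards no difference, with 30% appearing as about 27% at most in expectation. This rests on the 10% ceiling, the 23/45 chance and equal crossing in both directions; the true share is not given and could be well below 10%. The size is modest, but the bias is avoidable and the allocation rules need reconciling.

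**What to change.** 1. Before the lottery, choose the 40 households for intervention delivery and the 20 students' households for evaluation only from students whose home lies in the mapped catchment of the school they attend. Other students may still attend lessons with their class. Allocation follows baseline collection, so the choice cannot depend on arm.
2. State that the residence rule in Data analyses, item 1, applies to community and household outcomes, and that SR_S is analysed by the arm of the school randomised, as item 8 does for student KAP.

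The cost is some address checking earlier than planned, since the protocol maps the homes of participating students only. At the ceiling about 0.10 × 40 = 4 households per school need replacing. That is easy at the average of 250 sixth graders but less so in schools near the 40-student minimum in Table 1. Household results will describe students who live in their school's catchment. Traps and fish produced at school may still leak to some extent.
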